### Biological specimens

No biological specimens will be collected in the study.

### Monitoring and auditing

This study will be subject to on-site monitoring in accordance with the quality assurance advice of the Dutch Federation of University Medical Centres regarding research involving human subjects [67]. On-site monitoring will be based on the risk classification (negligible).

The sponsor/investigator will submit a summary of the progress of the trial to the ethics committee once a year. Information will be provided on the date of inclusion of the first subject, numbers of subjects included and numbers of subjects that have completed the trial, SAEs/serious adverse reactions, other problems, and amendments.

### Statistical analyses

#### Non-inferiority of blended CBT compared with face-to-face CBT at 20 weeks

Primary analyses will be on the basis of intention-to-treat (ITT) and per protocol using mixed model analysis in order to reduce the risk of falsely claiming non-inferiority of blended CBT [26, 27]. These analyses will be performed with the CIS20r fatigue severity score at the end of treatment (T20) as dependent variable and study group (blended vs. f2f CBT) as fixed factor. A graph showing CIS20r fatigue CIs and margins of non-inferiority will be used (see Fig. 3) [26, 27]. When blended care is found to be non-inferior, a sensitivity analysis will be performed on the basis of different assumptions about the values of missing data.

**Fig. 3 Fig3:**
[figure not shown]
Illustration of a possible result of the non-inferiority tria. Difference between face-to-face CBT and blended CBT and the 95% CI. H0: blended CBT is inferior to face-to-face CBT, meaning that face-to-face CBT – blended CBT ≥ M. Mis the non-inferiority margin (6.67–5.32 = 1.35). H1: blended CBT is non-inferior to face-to-face CBT, meaning that face-to-face CBT – blended CBT < Ml

To compare the effect of blended care and face-to-face CBT on the secondary outcome measures, the ITT mixed model analysis will be repeated with the secondary outcomes at the end of treatment (T20) as dependent variable and study group as fixed factor.

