### Sample size calculation

#### Non-inferiority trial (RCT 1)

If there is truly no difference between the face-to-face CBT and blended CBT, then 150 patients are required to be 80% sure that the lower limit of a one-sided 95% confidence interval (CI) will be above the non-inferiority margin of −5.3 points on the Checklist Individual Strength (CIS20r) fatigue severity subscale. Adjusting for a dropout of 10%, 166 participants need to be included (two groups of 83) [26–28]. The non-inferiority margin was defined on the basis of statistical reasoning (i.e., by using the TREFAMS-CBT results) and clinical judgement [16]. In the TREFAMS-CBT trial, the difference in the change score between CBT and MS nurse consultations for fatigue was 6.67 points (95% CI 2.70–10.68) on the CIS20r fatigue severity subscale [16]. In accordance with the recommendations of the US Food and Drug Administration [26], the following formula was used to derive the margin of non-inferiority: the mean effect 6.67 - 50% of the lower limit of the 95% CI of the TREFAMS-CBT effect at week 16 (i.e. 2.7), that is, 6.67–1.35 = 5.32. A 1.35 point loss in effectiveness of blended CBT compared with TREFAMS-CBT is considered as clinically acceptable [16]. Tummers et al. [28] derived the same non-inferiority margin of 5.3 points on the CIS20r fatigue severity subscale through post-hoc analysis of the course in the waiting list of an RCT testing the efficacy of CBT in patients with chronic fatigue syndrome. The margin of 5.3 points reflects the largest loss of effect in the blended CBT group that would be clinically acceptable.

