#### Primary outcome measure

In both RCTs, the primary outcome measure will be fatigue severity, as measured by the CIS20r fatigue severity subscale, either at the end of initial treatment (RCT 1: T20) or at 1 year (RCT 2: T52). At these time points, the differences in fatigue severity between both groups will be assessed. The same primary outcome measure is used as in the TREFAMS-CBT trial. The CIS20r is a 20-item self-reported questionnaire consisting of four subscales: (a) fatigue severity (eight items), (b) reduction in motivation (four items), (c) reduction in physical activity (three items) and (d) concentration problems (five items) [38, 50]. Items are answered on a 7-point Likert scale and added to a total score. The total score of the fatigue severity subscale can vary between 8 and 56 points. The CIS20r is a reliable and valid instrument for measuring fatigue in various study populations [39]. A cutoff score of 35 or higher is used to discriminate between severe fatigue and fatigue levels within the normal range.

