#### Secondary outcome measures

Clinical significant improvement assessed with the CIS20r is a secondary outcome measure. Clinical significant improvement is defined as either a score of less than 35 on the CIS20r fatigue severity subscale or an improvement of at least 8 points on this subscale [16]. As the CIS20r is also used as a screening tool thereby limiting the variance in the outcome measure, we decided to use the following additional fatigue measures as secondary outcome measures. The Fatigue Severity Scale (FSS) is used to measure the severity and impact of fatigue in patients with MS [51]. The FSS consists of nine items to be rated on a scale from 1 (strongly disagree) to 7 (strongly agree). The final score is the mean of all item scores. Also, the PROMIS-Fatigue Short Form 8a [52] is used to measure fatigue in addition to the CIS20r. This questionnaire consists of eight items to be rated on a scale from 1 (not at all/never) to 5 (very much/always). The final score is the sum score of all items.

The Sickness Impact Profile (SIP) [29, 30] will be used to measure limitations of daily functioning in eight different domains of functioning. The eight subscale scores are summed to provide one weighted score of disability (SIP8 total score). The SIP was used in several intervention studies with chronically fatigued patients. The Work and Social Adjustment Scale (WSAS) [53] is used to measure restrictions in participation. The WSAS is a five-item scale rating impairment on five different domains of functioning on a scale from 1 (not at all impaired) to 8 (severely impaired). The final score is the sum of all items. Health-related quality of life will be assessed by the SF36 [46], consisting of 36 items and eight subscales. Raw scores on each scale are converted to a score on a scale of 0 to 100, and a higher score indicates a higher level of well-being.

For these secondary outcome measures, no margins of non-inferiority have been defined. The course of the scores on these secondary outcome measures during the whole study year will be plotted for the various subgroups of participants. See Additional file 2: Table S2 for specifications of the primary and secondary outcome measures.

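### On the analysed T20 CIS20r score, where higher is worse, the Fig. 3 hypotheses run backwards; the scale and order of subtraction that would make them right are not stated

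*Protocol article*

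**What the plan says.** Four places in the protocol article bear on the direction of the RCT 1 decision rule.

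- **Statistical analyses, non-inferiority at 20 weeks.** The analysed variable is the "CIS20r fatigue severity score at the end of treatment (T20) as dependent variable". This is the score itself, not a change or a reduction. The same section describes Fig. 3: "A graph showing CIS20r fatigue CIs and margins of non-inferiority will be used".
- **Primary outcome measure.** "The total score of the fatigue severity subscale can vary between 8 and 56 points", and "A cutoff score of 35 or higher is used to discriminate between severe fatigue and fatigue levels within the normal range". Higher is therefore worse. Secondary outcome measures agrees, since it counts as clinically significant improvement "a score of less than 35 on the CIS20r fatigue severity subscale or an improvement of at least 8 points".
- **Fig. 3 caption.** H0 (blended inferior) is face-to-face minus blended at or above M, where M is given as 6.67 − 5.32 = 1.35. The alternative reads "H1: blended CBT is non-inferior to face-to-face CBT, meaning that face-to-face CBT – blended CBT < Ml". The last symbol carries a stray letter and is read here as M.
- **Sample size calculation, RCT 1.** The lower limit of a one-sided 95% confidence interval "will be above the non-inferiority margin of −5.3 points". No order of subtraction is given. The margin is built from an earlier trial's between-group difference in change scores (6.67, benefit positive) and is explained as a loss of effect.

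**The concern.** A non-inferiority rule needs three things fixed together: the scale, the order of subtraction and the confidence limit that decides. The caption gives an order and an inequality. The analysis section gives a scale. Put together, they point the wrong way: a blended arm with more fatigue makes face-to-face minus blended negative, and every negative value is below a positive M.

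This is the primary decision rule of the first trial, and the analysis section says its approach is meant to guard against a false claim of non-inferiority. If the rule were applied as printed to the variable as printed, it would give no such protection. The direction should be settled in writing before the independent analyst, who works blinded to allocation, has results to interpret.

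**Working it through.** **Inputs.** Raw T20 CIS20r score, higher = worse (Primary outcome measure; analysis section). M = 1.35 (Fig. 3 caption) or 5.3 (sample size section); both are carried through. 150 evaluable patients (75 per arm), one-sided 95% limit, 80% power, true difference 0 (sample size section). No SD is stated.

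**Step 1: the plan's own figure.** The usual formula is n per arm = 2·SD²·(z₀.₉₅ + z₀.₈₀)² / margin². With n = 75 and margin 5.3:

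SD = 5.3 × √(75/2) / (1.645 + 0.842) = 13.05.

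Without a stated SD, 150 cannot be confirmed independently; this is only the SD that it implies. The RCT 2 statement (98% power, 75 per group, difference 6.7, two-sided 5%) implies SD = 6.7 × √(75/2) / (1.960 + 2.054) = 10.22. Below, SD 10.2 to 13.05 is an assumed range.

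**Step 2: sign check on the analysed score.** Take a face-to-face mean of 35 for illustration.

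- Blended 45 (10 worse): 35 − 45 = −10. This is below 1.35 and below 5.3, so H1, non-inferior, is met.
- Blended 25 (10 better): 35 − 25 = +10. This is above 1.35 and above 5.3, so H0, inferior, is met.

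**Step 3: which scale and order make each rule right.** Improvement means T0 minus T20. With equal baseline means, a difference in improvement is minus the difference in T20 scores.

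| Scale | Difference | Worse blended arm gives | Caption (difference < M) | Sample size rule (lower limit > −5.3) |
|---|---|---|---|---|
| T20 score | face-to-face − blended | negative | reversed | correct |
| T20 score | blended − face-to-face | positive | not the caption's order | reversed |
| Improvement | face-to-face − blended | positive | correct | reversed |
| Improvement | blended − face-to-face | negative | not the caption's order | correct |

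In no row are both rules correct. They agree only if both are on the improvement scale and the sample size section subtracts in the opposite order to the caption. Neither convention is written down.

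**Step 4: size of the effect.** SE = SD × √(2/75) = 1.67 to 2.13. Let δ be the true face-to-face minus blended difference in T20 score.

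- Literal caption rule (upper one-sided 95% limit of face-to-face − blended below M): P = Φ((M − δ)/SE − 1.645).
- Redirected rule (upper limit of blended − face-to-face below M): P = Φ((M + δ)/SE − 1.645).

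Worked case: SD 13.05, M = 1.35, blended 10 worse (δ = −10). Literal: Φ(11.35/2.13 − 1.645) = Φ(3.68) = 0.9999.

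| True state of blended arm | M | P(non-inferior), literal | P(non-inferior), redirected |
|---|---|---|---|
| 10 points worse | 1.35 or 5.3 | 0.9999 or more | 0.0001 or less |
| worse by exactly M | 1.35 | 0.35 to 0.49 | 0.05 |
| worse by exactly M | 5.3 | above 0.999 | 0.05 |
| no difference | 1.35 | 0.16 to 0.20 | the same |
| no difference | 5.3 | 0.80 to 0.94 | the same |
| 10 points better | 1.35 or 5.3 | 0.0001 or less | 0.9999 or more |

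At no true difference the two rules have equal power, including the planned 80% at SD 13.05 and M = 5.3. Redirecting the rule therefore leaves the sample size as it is.

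**The case against.** The best defence is that the caption names treatments, not scores. It sits beside a margin computed from 6.67 and 5.32. The 6.67 is a benefit-positive difference in change scores, and the sample size section speaks of effect lost in the blended arm. If the caption means treatment effects, face-to-face minus blended is the effect lost, and its hypotheses are correct. The sample size rule then agrees in direction, read as blended minus face-to-face. Both hypotheses are also stated in words, the figure itself is not shown and might label its axis, and blinding hides the arm labels but not the fact that higher CIS20r is worse.

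Much of this stands. It makes the improvement scale a plausible intention. It also blocks two stronger readings that a reader might infer. One is that the trial would in practice reward harm: the verbal hypotheses point the right way, and nothing shows that the analysts would follow the symbols against the words. The other is that the sample size section flatly contradicts Fig. 3: that section gives no order of subtraction, so the conflict exists only if the caption's order is assumed for both.

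The defence does not cure the text. Neither the analysis section nor the caption mentions improvement, and the analysis section names the T20 score as the analysed variable and says the figure shows CIS20r fatigue intervals.

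**Conclusion.** The point holds as a fault in how the primary hypotheses are written. On the only analysis scale that the article states, the caption's inequality is reversed for any positive M: a blended arm truly 10 points worse would meet it with probability of about 1, and one 10 points better almost never. The sign result needs no assumption beyond that scale. The probabilities also assume 75 per arm, a normal approximation, a one-sided 95% limit and an SD between 10.2 and 13.05.

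The caption is right only on an improvement scale that the margin derivation suggests but that neither the analysis section nor the caption states. The finding does not say that a wrong analysis is planned, and only the caption could be checked. It also does not say which margin applies; the reversal occurs with 1.35 and with 5.3. Because it touches the primary decision rule and is easily repaired, it should be corrected before the analysis.

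**What to change.** State the scale and the order of subtraction once, and use them in the RCT 1 sample size section, the 20-week analysis section and the Fig. 3 caption. For example:

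- D = mean T20 CIS20r fatigue score, blended minus face-to-face; positive = blended worse.
- H0: D ≥ M. H1: D < M, with M > 0.
- Non-inferiority is declared if the upper confidence limit of D is below M.

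The sample size wording then changes from a lower limit above a negative margin to an upper limit below M, and the axis of Fig. 3 should say which side favours which arm. If the improvement scale is preferred, define it explicitly and turn the inequality to match.

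Keep M as a symbol in this correction. The caption gives 1.35 and the sample size section 5.3; writing either number in here would silently settle a separate conflict that must be reconciled on its own.

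The cost is a few lines of text and an axis label. The direction change alters neither the sample size nor the data to be collected.

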#### Effectiveness of CBT booster sessions at 52 weeks

Primary analysis of long-term effects of additional booster sessions will be based on ITT using mixed model analysis with CIS20r fatigue severity 1 year after the start of treatment (T52) as dependent measure and condition (booster session vs. no booster sessions) as fixed factor. In case of a large attrition rate, a per-protocol analysis will be added.

To compare the effect of booster sessions on the secondary outcome measures, the ITT mixed model analysis will be repeated with the secondary outcomes at T52 as dependent variable and study group as fixed factor.

In a separate analysis, we will additionally investigate the differential effect of the booster sessions in patients who are no longer severely fatigued at T20 compared with those who are still fatigued at T20.

Analyses of factors mediating long-term effectiveness will be conducted. In addition, analyses will be carried out to identify possible moderators of the response to the booster sessions and response to face-to-face or blended CBT.

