**Methods/design:**

The first part of this study is an observer-blinded non-inferiority multicentre RCT, in which 166 severely fatigued MS patients will be randomly assigned (1:1 ratio, computer-generated sequence) to either face-to-face CBT or blended CBT (MS Fit) for fatigue. The primary endpoint is at 20 weeks after baseline. After this post-treatment assessment, patients will be randomly assigned again (1:1 ratio, computer generated sequence) to either MS Stay Fit consisting of two booster sessions at 2 and 4 months after end of treatment or no booster sessions. The primary endpoint of the second study is 52 weeks after baseline. Primary outcome measure in both studies is fatigue severity assessed with the fatigue severity subscale of the Checklist Individual Strength (CIS20r). Outcomes will be assessed at baseline (T0), at the end of treatment (T20), and after 39 and 52 weeks (T39 and T52).

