### Participant retention

Participants receive the questionnaires online. For optimal retention, participants will be contacted by email or phone by the research assistant when they have not started the completion of the questionnaires within 1 week. Randomization is carried out after completing all questionnaires at T0 (R1) or T20 (R2), preventing missing data at these important moments. When participants are not willing to complete all measurements at T20, T39 or T52, they are asked to at least fill in the fatigue subscale of the CIS20r, which the primary outcome measure.

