### Participant withdrawal

Patients can leave the study at any time for any reason if they wish to do so without any consequences. Nevertheless, these patients are requested to fill in a final CIS20r fatigue. The researcher can withdraw a patient from the study in case of incorrect enrolment of the participant. Withdrawing from the study does not necessarily mean the patient has to stop treatment. The treating physician or the treating psychologist can decide to withdraw a patient from the study for urgent (medical) reasons. These reasons will be documented.

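### RCT 2 answers high attrition with an added per-protocol analysis, which recovers no missing T52 score, and its primary model as worded makes no use of T39

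*Protocol article*

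**What the plan says.** The section on the effectiveness of CBT booster sessions at 52 weeks sets an intention-to-treat mixed model "with CIS20r fatigue severity 1 year after the start of treatment (T52) as dependent measure and condition" (booster or no booster) as the fixed factor. It names no time term, no T39 outcome and no T20 covariate. On attrition it says: "In case of a large attrition rate, a per-protocol analysis will be added". It does not say what rate counts as large.

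For RCT 1, the section on non-inferiority at 20 weeks provides that, if blended care is found non-inferior, "a sensitivity analysis will be performed on the basis of different assumptions about the values of missing data". The RCT 2 section has no counterpart.

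On data collection, the abstract states: "Outcomes will be assessed at baseline (T0), at the end of treatment (T20), and after 39 and 52 weeks (T39 and T52"). T39 therefore falls within RCT 2 follow-up. Under Participant retention, "Randomization is carried out after completing all questionnaires at T0 (R1) or T20 (R2), preventing missing data at these important moments", so every patient entering RCT 2 has a T20 score. Patients unwilling to complete a full T20, T39 or T52 assessment are dealt with as follows: "they are asked to at least fill in the fatigue subscale of the CIS20r". Under Participant withdrawal, "these patients are requested to fill in a final CIS20r fatigue". The article does not say how that last score would enter the T52 analysis.

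**The concern.** Attrition is a problem of missing outcomes. A per-protocol analysis deals with something else, departures from the assigned treatment. Restricting the comparison to adherent patients leaves each missing T52 score missing and removes further randomised patients. It also compares groups that randomisation no longer balances. Under the plan it is brought in when attrition is high, which is when selection is already most troublesome.

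The model wording adds to this. With one outcome per patient and no time term, a patient last seen at T39 supplies no information on T52, even though the T20 and T39 scores are in hand.

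Selective loss is plausible on the protocol's own assumptions. The RCT 2 sample size section expects fatigue without boosters to drift back towards baseline while the booster arm keeps its gain. Only the booster arm has scheduled therapist contact at 2 and 4 months after treatment. If dropout is related to fatigue, the pattern could differ between arms, and the T52 comparison among those observed could then be off.

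**Working it through.** **What each analysis does with a re-randomised patient lacking a T52 score**

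| Analysis | Use of T20 and T39 | Effect on the missing T52 score |
|---|---|---|
| Primary model, read literally | none | patient contributes nothing |
| Added per-protocol analysis | none stated | still missing; non-adherent patients also removed |
| Mixed model of T39 and T52 with T20 as covariate | both used | patient informs the T52 contrast under missing at random |
| Sensitivity analysis on missing values | depends on the method | unobserved scores varied explicitly |

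**Inputs for size.** From the documents: expected difference 6.7 points, 75 per arm at 1 year, 10% attrition, two-sided 5%, stated power 98%. The article states no figure for dropout bias, so there is none to reproduce. It also gives no SD, so two implied values are used:

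- From RCT 2: SD = 6.7 × √(75/2) / (1.960 + 2.054) = 10.2. This is the SD at which the stated 98% power is reproduced.
- From RCT 1 (margin 5.3, one-sided 5%, 80% power, 75 per arm): SD = 5.3 × √(75/2) / (1.645 + 0.842) = 13.05.

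**Rough bias.** If dropouts score g points worse than completers, each arm's completer mean lies below its full mean by (dropout rate × g). The between-arm difference is therefore shifted by (difference in dropout rates) × g. Assume g = 6.7 to 10 and a 10-percentage-point imbalance:

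- 0.10 × 6.7 = 0.67 points
- 0.10 × 10 = 1.0 point

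Around an average of 10%, that imbalance means 5% in one arm and 15% in the other.

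**Simulation.** Assumptions: correlation 0.6 between visits; true T52 difference (no booster minus booster) 6.7, with half of it present at T39; dropout after T39 depending on the T39 score with logistic slope ±1 per SD; 10% attrition fixed in each arm.

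| Dropout mechanism | T52-only difference, SD 10.2 | SD 13.05 | Bias |
|---|---|---|---|
| Same in both arms | 6.70 | 6.72 | about 0 |
| More fatigued lost in booster arm; unrelated to fatigue in the other | 7.25 | 7.43 | 0.55 to 0.73 |
| Opposite directions in the two arms | 7.82 | 8.12 | 1.12 to 1.42 |

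Swapping the arms reverses the sign. Using T20 and T39 for all re-randomised patients gave 6.70 to 6.73 in these cases. That is expected, since the simulated dropout is missing at random given T39.

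A variant applies one fatigue-dependent rule with the same intercept to both arms, so that the more fatigued no-booster arm loses more patients. With a T39 difference of 4.5 to 6.7 and correlation 0.6 to 0.7, the T52-only difference falls from 6.7 to about 6.4 to 6.5 at 10% overall attrition. Here the booster effect is understated.

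**Precision.** Let m be the fraction missing T52 and r the T39–T52 correlation (assumed 0.7). Variance relative to complete data:

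- T52 only: 1/(1 − m) = 1.111 at m = 10% and 1.176 at m = 15%.
- With T39: (1 − r²)/(1 − m) + r² = 0.51/0.90 + 0.49 = 1.057, and 0.51/0.85 + 0.49 = 1.090.
- Reduction in standard error: 1 − √(1.057/1.111) = 2.5%, and 1 − √(1.090/1.176) = 3.7%.

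This is the best case, because it takes T39 as observed for everyone missing T52.

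**The case against.** The strongest reply has five parts.

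- **The model is under-described.** The article condenses a fuller protocol. A mixed model suggests some repeated or clustered structure, and naming T52 may only identify the contrast to be tested. A reader might infer that the plan throws away T39 scores and runs a complete-case analysis. The article does not say so; it follows only from the literal wording. This part stands.
- **Prevention is planned.** Reminders, the fatigue-only minimum, the final score at withdrawal, a complete T20 before re-randomisation and a 10% attrition allowance all bear on the problem. A reader might infer that missing outcomes are ignored altogether; that is not supported. These are collection and sample size measures, however, and do not settle how scores that are still missing are analysed.
- **The per-protocol analysis is only added.** Intention-to-treat remains primary, so the extra analysis cannot distort the primary result. A pooled attrition rate can also be judged blind to treatment effect, and the analyst is blinded to allocation. Both stand. The missing threshold and the mismatch between remedy and problem remain.
- **RCT 1 is not a clean benchmark.** Its missing-data analysis is conditional on a finding of non-inferiority, and the extra caution there is motivated by that design. The absence of a counterpart in RCT 2 could be detail left to the full plan and is not by itself an error. The objection here is to the remedy that the article does state.
- **Bias may be nil or conservative.** If relapsing patients are lost mainly from the no-booster arm, the booster effect is understated. A reader might infer that the T52 result will be biased in favour of boosters; the documents do not support that.

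**Conclusion.** The point holds in a limited form. The stated response to attrition does not address attrition, and its trigger has no threshold. The primary model, as worded, makes no use of T39, and the text should say whether that is meant.

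The likely damage at the planned attrition is modest: about 0 to 1.4 points in either direction at 10%, against an expected 6.7, and a standard error at most about 2.5 to 4% longer than it need be. The bias figures rest on assumed correlations, SDs and dropout mechanisms, none of which the documents give. The upper end needs dropout to work in opposite directions in the two arms. The main reason to act is that a cheap and better-matched analysis is available from scores already scheduled for collection.

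**What to change.** 1. State the RCT 2 primary analysis as a mixed model of CIS20r fatigue at T39 and T52 with condition, time and condition-by-time, and the T20 score as covariate. Include every re-randomised patient with any score after the second randomisation, and test the T52 contrast. If this was already intended, say so.
2. Replace the attrition-triggered sentence with a sensitivity analysis under different assumptions about missing T52 scores, for example delta-adjusted, performed whatever the primary result and whatever the attrition rate.
3. If a per-protocol analysis is kept, define it by adherence to the assigned condition and label it supplementary.

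The cost is revised wording and a little more analysis work. No new data or visits are needed. At submission of the article 64 of 166 patients had been randomised.
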